### Statistical Analyses

These will be blinded and will be performed in consultation with a statistician. Baseline and demographic data will be presented using descriptive statistics. Differences from baseline will be calculated for all primary and secondary outcomes. Mean differences, standard deviations and 95% confidence intervals will be calculated for all continuous outcomes. A longitudinal repeated measures design will be used to assess change from baseline and to make between group comparisons for the continuous outcome measures. Comparisons will be made between the 3 groups at the 9 week period. Participants in the control group will be analysed according to the intervention received after the 9 week follow-up and comparisons will be made between the 2 intervention groups at 18 weeks (both with and without the re-randomised control group subjects at the 18 week period). This will be done on an 'intention to treat' basis. Participants will be analysed in the intervention groups to which they were originally assigned and will include withdrawels and patients not treated by the assigned intervention. Missing data will be replaced using the last observation carried forward. Per-protocol analyses will also be performed by excluding patients with deviations from the treatment protocol.

At the 9 week and 18 week time points, continuous variables will be analysed using a mixed ANOVA model (with treatment as the between group factor and time as the repeated factor), or the non-parametric equivalent if non-normal distributions apply. Where significant differences occur, post-hoc comparisons will be conducted using Tukey's multiple comparison procedure. Differences in nominal/ordinal data will be analysed using the χ^2 ^test. A significance level of 0.05 will be set for any inferential statistics conducted.

Secondary analysis will be undertaken to assess the predictors of outcome at primary endpoint (9 weeks post treatment) in both intervention groups, using multiple regression analyses. A number of predictor variables such as age, gender, x-ray severity, baseline pain, physical function, mood, co-morbidities and treatment expectations will be measured. Analyses will be performed separately for exercise therapy, and combined exercise and manual therapy. Response variables will be change in WOMAC physical function score pre and post intervention (MCID> 5.4) and Global Assessment of Change. All predictors will be checked for collinearity. Univariate logistic regression will be performed on all potential predictors and those associated with the outcomes will be entered into the multivariate logistic regression model and backward regression will be performed. Variables with the lowest predictive value will be removed from the model if p > 0.05. Odds ratios and 95% confidence intervals will be calculated for all final predictors.

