## Methods

### Aim

The primary aim of this study is to compare the effect of a combination of manual therapy and exercise therapy, exercise therapy only and a waiting-list control on physical function in hip OA.

A secondary aim of the study will be to investigate the effect of baseline variables such as age, gender, body mass index, disease severity, baseline pain, physical function, mood and co-morbidities on treatment outcome.

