### Sample Size Considerations

The primary outcome measure-WOMAC physical function subscale- has been used to estimate the sample size required. The minimum clinically important difference (MCID) has been ascertained [66]. Using an MCID of 5.4 (SD = 11) on WOMAC Likert scale, with a significance level of 0.05 (2 tailed) and a power of 80%, it is estimated that 67 patients are required per group. To allow for 10% attrition at the 9 week follow-up, it is estimated that 74 patients will be required per group. However, as the waiting list control group will be re-randomised into 2 treatment groups after the 9 week follow-up, 50 patients per group will be required to give a total sample size of 150 patients.

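### The plan does not clearly fix which analysis of WOMAC function decides the trial: one passage points to week 9, while the sample size rests on the pooled week-18 comparison

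*Protocol article*

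**What the plan says.** All places are in the Protocol article.

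- *Aim*: the primary aim reads "compare the effect of a combination of manual therapy and exercise therapy, exercise therapy only and a waiting-list control on physical function in hip OA".
- *Sample Size Considerations*: "The primary outcome measure-WOMAC physical function subscale- has been used to estimate the sample size required". The inputs are a difference of 5.4 and an SD of 11, two-sided 0.05 and 80% power. They give 67 per group, or 74 with 10% attrition. The section then says that "as the waiting list control group will be re-randomised into 2 treatment groups after the 9 week follow-up, 50 patients per group will be required", 150 in total.
- *Statistical Analyses*, first analysis: "Comparisons will be made between the 3 groups at the 9 week period".
- *Statistical Analyses*, second and third analyses: "comparisons will be made between the 2 intervention groups at 18 weeks (both with and without the re-randomised control group subjects at the 18 week" (the source only completes the bracket).
- *Statistical Analyses*, error control: Tukey's procedure follows a significant result within an analysis, and "A significance level of 0.05 will be set for any inferential statistics conducted".
- *Statistical Analyses*, predictor paragraph: "Secondary analysis will be undertaken to assess the predictors of outcome at primary endpoint (9 weeks post treatment) in both intervention groups". Only here is a time point called primary.
- *Discussion*: the two interventions are compared with and without the former controls to gauge what the waiting period does to outcomes. It does not say which version leads.

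**The concern.** A primary outcome does not settle a trial until the contrast, the time point and the analysis set are also fixed. Here the question whether manual therapy adds to exercise is tested three times on the same scale: at week 9, at week 18 in the original arms, and at week 18 with former controls added. Tukey's procedure works inside one analysis. Nothing orders the three analyses or shares the 5% between them.

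This is more than detail left to an analysis plan, because two statements in the article pull apart. The only passage that names a primary time point says 9 weeks. The sample size is adequate only for the pooled comparison at 18 weeks. An analysis plan that settled the matter would have to depart from one of them.

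Two things are at stake. Authors who follow the text could present whichever of the three results is favourable. And if week 9 decides, the power stated for the trial does not apply to the deciding comparison.

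**Working it through.** **1. Reproduce the sample size.** Inputs from *Sample Size Considerations*: "Using an MCID of 5.4 (SD = 11) on WOMAC Likert scale", two-sided 0.05, power 80%.

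n per group = 2 × (1.960 + 0.842)² × 11² / 5.4² = 65.1, so 66. The t-test version gives 66.1, so 67, the article's figure. Attrition: 67 × 1.10 = 73.7, so 74 (dividing by 0.9 gives 74.4, so 75). Arms of 50 plus half of the 50 controls give 50 + 25 = 75 per intervention, and 2 × 75 = 150. The total therefore fits a comparison of the two interventions that includes the former controls.

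**2. Patients and power for each analysis.** Power is for a 5.4-point difference, SD 11, two-sided t-test at 0.05. The evaluable numbers apply the article's 10% attrition at both visits (an assumption for week 18): 50 × 0.9 = 45, and 45 + 22 = 67.

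| Analysis | Per group, all / evaluable | Power, all / evaluable |
|---|---|---|
| Week 9, one pair | 50 / 45 | 68% / 63% |
| Week 18, original arms | 50 / 45 | 68% / 63% |
| Week 18, pooled | 75 / 67 | 85% / 81% |

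With the planned overall test followed by Tukey, the week-9 figures fall to about 53% and 48% (third arm equal to one of the pair). Only the pooled week-18 analysis reaches the stated 80%.

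**3. What the 9-week phrase means.** *Outcome Measures* puts the end of treatment for the former controls at week 18, and calls their week-27 visit 18 weeks post treatment. Since 27 − 18 = 9, that count starts when treatment starts. By the same count, 9 weeks post treatment is week 9 for the original arms. Counted literally from the end of treatment, it would fall near week 18. Week 9 is the more natural reading, but the wording does not secure it.

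**4. False-positive rate if any of the three analyses could carry the trial.** For three independent tests, 1 − 0.95³ = 14.3%. These tests share patients, so the rate was simulated with no treatment effect. The correlation between week 9 and week 18 is not in the article and was varied. Change scores were tested separately at each visit, a simplification of the planned mixed ANOVA.

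| Correlation | 50 per arm, 75 pooled; overall F at week 9 | 45 per arm, 67 pooled; F then Tukey at week 9 |
|---|---|---|
| 0 | 12.3% | 11.8% |
| 0.3 | 12.2% | 11.6% |
| 0.5 | 11.9% | 11.3% |
| 0.7 | 11.2% | 10.8% |
| 0.9 | 10.6% | 10.5% |

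Other readings:
- manual versus exercise only, over its three tests: 8.2% to 9.3%;
- the two week-18 versions alone: about 7.7%;
- week 9 alone, F then Tukey: about 4.4% to 4.5%.

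**5. How often the choice would matter.** If manual therapy truly adds 5.4 points (SD 11) at both visits, the two week-18 versions disagree on significance in about 20% to 21% of trials.

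**The case against.** A reader might infer that the plan names no deciding comparison at all and that its false-positive rate simply is about 11%. The article does not support either statement.

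- The plan is not silent. The aim is a three-way comparison, three groups are compared only at week 9, and the predictor paragraph calls 9 weeks primary. Together these imply the three-group analysis at week 9, whose error rate is below 5%.
- The *Discussion* gives the with-and-without pair a purpose, to assess the waiting period. That is the role of a robustness check, not of two further chances of success.
- The 0.05 is a level for each test. The article states no trial-wide error rate that could be broken, and nowhere says that one success out of three makes the trial positive.
- Disagreement between the analyses partly reflects their different power. It is expected and does not by itself show an error in the plan.

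All of this stands, and it makes the 10% to 12% conditional. It does not remove the point. The week-9 reading has to be assembled from an aim and an aside in a secondary analysis, and neither names the contrast that decides. The *Discussion* does not say which week-18 version leads. And the sample size argues for a different analysis from the one the aim and the aside suggest.

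**Conclusion.** The concern holds as a mismatch. The article implies week 9 as the primary time point but justifies 150 patients through the pooled week-18 comparison, and no sentence says which decides.

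Its size depends on the reading. If any of the three analyses could carry the trial, the false-positive rate is about 10% to 12% (8% to 9% for manual versus exercise alone), over assumed correlations of 0 to 0.9. If week 9 alone decides, error is controlled at about 4% to 5%. The cost then appears in power: about 68% with 50 per arm or 63% with 45 evaluable for a pairwise difference of 5.4 points, and about 53% or 48% after the overall test and Tukey, against the 80% stated. This should be settled before the analysis.

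**What to change.** In *Statistical Analyses*, add a few sentences that:

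1. name one contrast, time point and analysis set for WOMAC physical function as confirmatory at two-sided 0.05. The aim and the predictor paragraph suggest the three groups as first randomised, at week 9, with Tukey for the pairs;
2. label the other analyses secondary or sensitivity, and name one lead version at week 18;
3. allow a week-18 claim only from that version, and only if the confirmatory contrast is significant.

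Then align *Sample Size Considerations* with the choice. If week 9 is confirmatory, replace the 80% with the week-9 power given above, stating the number per arm and whether Tukey is included. If the sponsor prefers the pooled week-18 comparison, the sample size can stand, but the predictor paragraph's reference to the primary endpoint must change and the three-group comparison becomes secondary.

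No patients or data are added. With week 9 as confirmatory, a result significant only at week 18 could no longer be the main finding, and the stated power would be less favourable.

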### Outcome Measures

Patients will be assessed at baseline, 9 weeks (end of treatment for the intervention groups) and 18 weeks (end of treatment for the control group) by the blinded assessor in the physiotherapy department of each hospital. Subjects in the control group will have an additional follow-up at 27 weeks (18 weeks post treatment) (Fig 1). Subjects and treating therapists cannot be blinded to treatment allocation due to the nature of the interventions.

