A distinctive feature of the study is the inclusion of a waiting-list control group. This is a variation of a cross-over trial, where the participants in the control group are crossed over to one of the intervention groups after the 9 week follow-up assessment. This design was chosen, as one of the inclusion criteria for participation in the trial was that all subjects must have been referred for physiotherapy, and consequently must receive treatment. As the waiting times for physiotherapy at the four participating sites can vary between 6–12 weeks, this waiting-list control group will not be unduly compromised in their waiting times for treatment. A true control group can result in higher dropouts as patient expectations are not met and implementing a cross-over design may help to reduce dropout rates in studies investigating chronic diseases such as arthritis [95]. The decision to include a control group was made because, although exercise therapy has been shown to have a positive short term effect on pain and function in hip OA, the specific exercise protocol in this study has not previously been investigated. Both exercise and manual therapy protocols are based on current clinical practice identified through questionnaire survey [19] and therefore should be easily implemented in a clinical setting. The waiting-list control group will improve the scientific rigour of the study and allows more definite conclusions to be made regarding the effect of the two interventions under investigation. The control group patients will be re-randomised into one of the two intervention groups after the 9 week follow-up. A similar design was used by Fransen et al [91,96]. Statistical analyses will be conducted on the two intervention groups, with and without the re-randomised control group subjects, to assess the effect of the 9 week waiting period on outcomes.

A combination of self-report and physical outcome measures will be used, all of which are easy to administer in a standardized manner across the four sites.

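### The pooled week-18 comparison mixes original-arm patients 9 weeks past treatment with re-randomised controls at end of treatment; it should be aligned on time since treatment began

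*Protocol article*

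**What the plan says.** The Outcome Measures section fixes the visits relative to treatment: "9 weeks (end of treatment for the intervention groups) and 18 weeks (end of treatment for the control group"). It adds one visit for the controls: "Subjects in the control group will have an additional follow-up at 27 weeks (18 weeks post treatment"). The Randomisation section has controls re-randomised to one of the two interventions, from a second list, after their week-9 assessment.

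The Statistical Analyses section compares all three groups at week 9. It then states that "comparisons will be made between the 2 intervention groups at 18 weeks (both with and without the re-randomised control group subjects" at that period). It describes no other pooled comparison and gives the week-27 visit no role. The Discussion gives the purpose of the two versions: "with and without the re-randomised control group subjects, to assess the effect of the 9 week waiting period on outcomes".

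The Sample Size Considerations section starts from a target: "Using an MCID of 5.4 (SD = 11) on WOMAC Likert scale". It continues: "with a significance level of 0.05 (2 tailed) and a power of 80%, it is estimated that 67 patients are required per group". It then adds: "To allow for 10% attrition at the 9 week follow-up, it is estimated that 74 patients will be required per group". The number randomised per group is cut to 50 because the controls will be re-randomised. No time point is named for the powered comparison.

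**The concern.** Pooling by calendar week puts patients at two different stages into each arm. About two thirds of an arm would show what remains 9 weeks after treatment stopped, and about one third would show the immediate result. Unless the added effect of manual therapy is the same at both stages, the pooled difference matches neither question a clinician would ask.

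This matters because the re-randomised controls are what bring each intervention up to the required number. The stated check on the waiting period is affected too. Original and re-randomised patients differ at week 18 in whether they waited and also in time since treatment, so comparing results with and without the controls cannot separate the two. The week-27 visit, which would bring the controls to the same stage as the original arms at week 18, is used in no stated analysis.

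**Working it through.** **Inputs.** From Sample Size Considerations: difference 5.4, SD 11, two-sided alpha 0.05, power 80%, 10% attrition at week 9, 50 per group in three groups. From Outcome Measures: treatment ends at week 9 (original arms) and week 18 (re-randomised controls).

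**1. The plan's own figure.** n = 2 × [SD × (1.960 + 0.842) / 5.4]² = 65.1 per group, so 66 by the normal approximation. The two-sample t-test gives 66.1, so 67, as stated. Attrition: 67 × 1.1 = 73.7, so 74, as stated (67 / 0.9 = 74.4 would round up to 75).

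**2. Where 74 per group comes from.** Each intervention has 50 original patients plus about 50 / 2 = 25 re-randomised controls, so about 75. Without the controls, t-test power for 5.4 is 68% with 50 per arm, or 63% with 50 × 0.9 = 45 per arm.

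**3. Stage of treatment at each visit.**

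| Visit | Original arms | Re-randomised controls |
|---|---|---|
| Week 9 | end of treatment | before treatment |
| Week 18 | 18 − 9 = 9 weeks after end | end of treatment |
| Week 27 | no visit stated | 27 − 18 = 9 weeks after end |

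The matching pairs are week 9 with week 18, and week 18 with week 27. The plan pools within the week-18 row.

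**4. What the pooled difference estimates.** Weights are 50/75 = 2/3 and 25/75 = 1/3:

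pooled difference = 2/3 × (effect 9 weeks after end) + 1/3 × (effect at end of treatment).

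**5. Size.** Assumption: the added effect of manual therapy is 5.4 at end of treatment and a share r remains 9 weeks later. The pooled difference is then 5.4 × (2r/3 + 1/3). Power is from the two-sample t-test with SD 11 and 67 per arm (75 × 0.9 = 67.5, rounded down).

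| Share r remaining | Effect 9 weeks later | Pooled difference | Power, pooled week 18 | Power, aligned end of treatment |
|---|---|---|---|---|
| 1 | 5.4 | 5.4 | 80% | 80% |
| 0.75 | 4.05 | 4.5 | 65% | 80% |
| 0.5 | 2.7 | 3.6 | 47% | 80% |
| 0.25 | 1.35 | 2.7 | 29% | 80% |
| 0 | 0 | 1.8 | 16% | 80% |

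The documents do not say which row applies. An aligned follow-up analysis (week 18 with week 27) would not rescue power if the effect fades: 56% at r = 0.75 and 29% at r = 0.5. It would, however, estimate a defined quantity.

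**6. Chance variation in the mixture.** Simple randomisation is stated for allocation and is assumed here for the second list. Simulation then puts the re-randomised share of an arm between about 23% and 44% (95% range), and the difference in share between arms within about ±15 percentage points. This supports including cohort in the model.

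**The case against.** The strongest reply is that nothing here is biased. Both allocations come from independently generated lists, so the two pooled arms have the same expected mixture. If the added effect is stable, the pooled contrast equals both effects. The original arms alone also give each unmixed effect, at week 9 and at week 18. This stands: the loss is in clarity and power, not validity. It is not a full answer, because the unmixed comparisons have only 63–68% power for 5.4.

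A reader might infer from the Background that the effect will fade, so that the low-power rows are to be expected. The documents do not support that. The Background describes the benefit of exercise as short-term, and both arms receive exercise. It says nothing about how long the added effect of manual therapy lasts. A reader might also add a second 10% loss between weeks 9 and 18. The plan states only one, at week 9, and carries the last observation forward.

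A reader might call pooled week 18 the declared main test of manual therapy. The plan names 9 weeks as the primary endpoint and gives no time point for the powered comparison. The link is an inference from there being only one pooled comparison.

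Three further points are weaker than they look:
- **Labels.** Week 27 is 9 weeks after the controls' treatment ends but 27 − 9 = 18 weeks after it begins. Counted from the start, this label and the 9-week label for the primary endpoint agree. That is loose wording, and may mean that alignment was intended.
- **Grouping.** Controls are to be analysed by the intervention received, while under intention to treat "Participants will be analysed in the intervention groups to which they were originally assigned". The natural reading is the arm assigned at re-randomisation, so a break of the second randomisation should not be inferred.
- **Baseline.** The controls' 9 untreated weeks precede re-randomisation and are balanced between arms in expectation. At most, precision suffers.

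**Conclusion.** The concern holds in a limited form. As written, the only pooled comparison is a randomised but mixed estimate: about 2/3 follow-up effect and 1/3 end-of-treatment effect. It equals either one only under a constancy assumption that the protocol does not state. With 5.4 at end of treatment, SD 11 and 67 per arm, power runs from about 80% (full persistence) down to 16% (none). These figures rest on the assumed share remaining, and on the inference that this is the powered comparison.

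Two parts need no assumption about size. The comparison with and without controls cannot isolate waiting, because waiting is confounded with time since treatment. The week-27 visit has no stated analysis. A reader might conclude that the manual-therapy comparison is invalid or bound to be underpowered; neither follows from the documents.

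**What to change.** In Statistical Analyses, define the pooled comparison by time since the start of allocated treatment:
- **End of treatment:** original arms at week 9 with re-randomised controls at week 18.
- **Follow-up:** original arms at week 18 with re-randomised controls at week 27.
- **Baseline:** use the controls' week-9 score as their pre-treatment value.
- **Grouping:** analyse re-randomised controls by the arm assigned on the second list.
- **Model:** include cohort (original or re-randomised) as a factor, with a cohort-by-treatment term to examine waiting.
- **Sensitivity:** keep the version without the re-randomised controls.

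In Sample Size Considerations, state which comparison and time point are powered. Amend the Discussion so that the waiting period is assessed through the aligned model. In Outcome Measures and the predictor paragraph of Statistical Analyses, say whether the post-treatment labels count from the start or the end of treatment.

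No extra patients or visits are needed. The cost is a change of analysis wording and slightly more analysis work.

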### Evidence for Exercise Therapy

Therapeutic exercise has been recommended as a key component of the management of hip OA in a number of clinical guidelines [20-24]. It can comprise joint-specific exercise for range of motion, strengthening of muscles around the hip and general aerobic conditioning. It can take place on land or in water (hydrotherapy) and can be done in a supervised setting or as a home-based self-directed programme [25]. A number of studies have evaluated the effect of exercise therapy in hip OA. Different forms of exercise therapy have been investigated such as hydrotherapy [26-30] and strengthening [29,31-34]. Exercise has also been used as a control intervention with the provision of advice/education and a programme of home exercises [28,35].

Although a number of systematic reviews have been undertaken evaluating the effectiveness of exercise therapy in OA, most of these have included knee and hip OA studies [36-39], with just one focussing specifically on hip OA [40]. This review, based on nine RCTs, found that therapeutic exercise, with a strengthening component, was an efficacious treatment for pain in hip OA. To date, the benefits of exercise for improving pain and function in hip OA appear to be short-term only [32,34,38] However, many of the studies undertaken have combined hip and knee OA patients [29,30,32,41] thereby limiting the value of the results. These studies were not powered sufficiently to observe the effect of exercise on hip OA only. Secondly, the same exercise regime was used by patients with hip and knee OA, thus the specificity of the exercise regime to hip OA is questionable. Certain flaws existed in many of the studies such as inadequate sample size [29,34], lack of intention-to-treat analysis [41,42] and lack of blinding of outcome assessors [29,42]. Due to the nature of exercise based interventions, blinding of the subjects and treating therapists was not possible in any of the studies [43].

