### Control Group (Waiting List Control)

Participants in the control group will continue to wait on the physiotherapy waiting list for an eight week period. On the 9^th ^week, they will complete a follow-up assessment with the blinded outcome assessor. They will then be re-randomised into one of the two intervention groups.

All groups will receive standardized written information on hip OA as recommended by clinical guidelines [22] including a standardised educational booklet entitled 'Osteoarthritis: helping you to understand osteoarthritis' and 'Osteoarthritis-Questions and Answers' published by Arthritis Ireland. This will ensure that education is not a confounding variable in the study.

All non-consenting and excluded participants will be treated as usual by the physiotherapy department of each trial centre. Participants will be asked to avoid all other forms of intervention for the duration of the RCT, apart from routine doctor care and analgesics. Participants with bilateral hip OA will receive treatment for both hips, but outcomes will be assessed on the worst affected hip only.

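### Last observation carried forward scores week-9 dropouts as unchanged and, in one 18-week analysis, counts untreated control scores as treatment outcomes

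*Protocol article*

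**What the plan says.** The Statistical Analyses section sets an intention-to-treat analysis that keeps withdrawals, and then gives one rule for gaps: "Missing data will be replaced using the last observation carried forward". The per-protocol analysis that follows deals with treatment deviations, not with missing scores.

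The schedule under Outcome Measures decides what can be carried: "Patients will be assessed at baseline, 9 weeks (end of treatment for the intervention groups) and 18 weeks (end of treatment for the control group". Nothing is measured between baseline and week 9. Sample Size Considerations expects losses at that visit: "To allow for 10% attrition at the 9 week follow-up". The paragraph on predictors attaches the term primary endpoint to nine weeks, which I read as the week-9 assessment.

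For controls, the waiting-list section says "Participants in the control group will continue to wait on the physiotherapy waiting list for an eight week period". They are assessed in week 9, and "They will then be re-randomised into one of the two intervention groups". The 18-week comparison of the two interventions is run "both with and without the re-randomised control group subjects at the 18 week period".

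**The concern.** Carry-forward has different consequences at each visit of this schedule.

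- **Week 9, all arms.** For an outcome with a baseline, the only earlier score is the baseline. The rule therefore assigns exactly zero change to everyone missing at week 9.
- **Week 18, re-randomised controls.** Their last score before week 18 was taken while they were still untreated. If week 18 is missing, that score is analysed as the result of the intervention they were later assigned.
- **Week 18, original arms.** An end-of-treatment score is held fixed to week 18, although the Background says "the benefits of exercise for improving pain and function in hip OA appear to be short-term only".

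In each case the filled-in value is then analysed as if observed. At stake are the estimated effect at the main time point, the honesty of its confidence interval and, if dropout differs between arms, the type I error. Unequal dropout is conceivable: participants know their allocation, and the Discussion acknowledges that an untreated control group can lose more people, a risk the delayed-treatment design is meant to reduce.

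**Working it through.** **Inputs.** From Sample Size Considerations: difference 5.4, SD 11, two-sided 0.05, power 80%, 10% attrition at week 9, 50 per arm. Assumptions of mine: SD 11 is the SD of change (the article does not say), dropout is unrelated to response, and control change is zero unless stated. Dropout rates other than 10% are illustrative.

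**1. The plan's own figures.** n = 2 × 11² × (1.960 + 0.842)² / 5.4² = 65.1, so 66 by the normal formula; the t-based value is 66.1, so 67. For attrition, 67 × 1.10 = 73.7, so 74 (67 / 0.90 = 74.4 would give 75). The stated 67 and 74 reproduce. The checks below use the 50 per arm actually planned.

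**2. Week-9 estimate.** With dropout d and mean improvement m, the carry-forward mean in an arm is (1 − d)m. At 10% in both arms: 0.9 × 5.4 − 0.9 × 0 = 4.86, a bias of 0.54 towards zero.

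**3. Week-9 standard error.** The variance of change in an arm is (1 − d)SD² + d(1 − d)m².
- Treated: 0.9 × 121 + 0.09 × 29.16 = 111.52
- Control: 0.9 × 121 = 108.90
- Carry-forward SE: √((111.52 + 108.90) / 50) = 2.10
- Observed-data SE: 11 × √(2/45) = 2.32
- Ratio: 0.905, so about 9.5% smaller

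**4. Size by dropout rate**, equal in both arms; coverage from 20,000 simulated trials:

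| Dropout | Estimate | SE, carry-forward | SE, observed | Ratio | Coverage of 95% interval |
|---|---|---|---|---|---|
| 10% (plan) | 4.86 | 2.10 | 2.32 | 0.905 | 94.2% |
| 20% | 4.32 | 1.99 | 2.46 | 0.81 | 91.3% |
| 30% | 3.78 | 1.87 | 2.63 | 0.71 | 85.6% |

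At 10%, simulated power is 0.637 with carry-forward and 0.640 with observed data.

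**5. Unequal dropout, no true difference.** Let both arms improve by 5.4.
- 5% against 20%: 0.95 × 5.4 − 0.80 × 5.4 = 0.81 of spurious difference; type I error 6.7%.
- 10% against 30%: 4.86 − 3.78 = 1.08; type I error 8.3%.

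The observed-data analysis stays near 5% in both. The false advantage goes to the arm that loses fewer people, so swapping the rates reverses its sign.

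**6. Re-randomised controls at week 18.** With 10% lost by week 9, 45 of 50 controls remain, or 22.5 per intervention. If a further 10% were lost (assumed; the article gives no rate for weeks 9 to 18), 2.25 per arm would carry an untreated score; starting from 25 per arm it would be 2.5. Carried untreated scores differ by zero on average between the re-randomised arms. An assumed true difference of 5.4 between interventions would therefore become 5.4 × 0.9 = 4.86 in this cohort and (50 × 5.4 + 25 × 4.86) / 75 = 5.22 when pooled with the original arms, counting only this mechanism. At 20% lost, the figures are 4.32 and 5.04.

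**7. Original arms at week 18.** If benefit fades by f after week 9 and a share d is carried forward, with dropout unrelated to fading, the within-arm change is overstated by d × f. The between-arm contrast is biased by d₁f₁ − d₂f₂, which is zero when dropout and fading are equal.

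**The case against.** The strongest reply is that little happens at the plan's own rate: 0.54 points, coverage close to nominal, power almost unchanged. That stands. The lower coverage figures and the inflated type I errors depend on dropout rates the article does not give. It is also true that the carry-forward standard error correctly describes the spread of the carry-forward mean; it is too small only relative to the information actually observed on the treatment effect.

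The re-randomised-control fault is contained as well. It touches neither the three-group comparison at week 9 nor the 18-week comparison without these participants.

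A reader might go further in three ways that the document does not support:

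- **That week-18 carry-forward tilts the comparison towards lasting benefit.** By then the planned contrast is between two interventions, with no untreated arm. The Background speaks of short-lived exercise benefit, not of fading that differs between the two treatments. Only the within-arm change can be called overstated on this ground.
- **That the rule is safely conservative.** Step 5 shows that it is not when dropout is unequal.
- **That every outcome is set to zero change.** The Global Assessment of Change has no baseline, so there is nothing to carry to week 9.

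**Conclusion.** The concern holds in limited form. Carry-forward is a stated rule, and with this visit schedule it gives wrong values in two identifiable places: zero change for participants missing at week 9, and untreated scores counted as intervention outcomes in the 18-week analysis that includes re-randomised controls.

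At 10% equal random dropout the first costs about a tenth of the effect and understates the standard error by 9 to 10%. This rests on no control change and on reading SD 11 as the SD of change. The second would affect about 2 to 3 participants per arm under an assumed further 10% loss. The direction of bias is not fixed once dropout is unequal. The plan should be changed on this point, but the article gives no ground for saying that the rule by itself would overturn the trial's conclusions.

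**What to change.** Replace the carry-forward sentence as follows.

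- **Primary analysis.** Use a likelihood-based linear mixed model on observed scores, with no carry-forward. Include baseline as a response with its mean constrained equal across arms, or use multiple imputation. If baseline were only a covariate, a participant with nothing but a baseline score would contribute nothing to the treatment effect. Treating it as a response keeps these people in the model, though it cannot create information they did not supply.
- **18-week analysis with re-randomised controls.** Analyse them in the arm of their second randomisation, use the week-9 score as their pre-treatment baseline, and stratify by cohort (original or re-randomised). A week-9 control score should never stand as a post-treatment outcome.
- **Sensitivity.** Keep carry-forward at most as a sensitivity analysis, still subject to that restriction. Add a shift (delta) analysis to explore departures from missing at random.

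The cost is a few sentences and standard software; a longitudinal repeated-measures analysis is already planned. The small downside is reliance on missing at random. The shift analysis shows how far conclusions depend on that assumption but cannot verify it.
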